### Descriptive statistics

Descriptive statistics tables will be generated to summarize the characteristics of the participants. The number of participants included and excluded will be reported. Among the included participants, the information will be broken down by site, sex, and age group. Results will be reported either in absolute numbers (e.g. number of subjects in a group) or summarized by mean, median, standard deviation, minimum, maximum and quartiles.

### Efficacy analyses

The point estimates of the study outcomes (percentage of antibiotic use, percentage reduction from baseline), with a 95% confidence interval based on the Wilson score interval, will be calculated for (1) clinical outcome (favourable or unfavourable), (1a) between-arms and (1b) between compliant and compliant patients within arms and for (2) antibiotic use, also (2a) between-arms and (2b) within-arms.

### Analysis of endpoints

The endpoints of the trial will be evaluated as follows:
The proportion of cases with a favourable outcome in the two arms, in the mITT and PP populationThe proportion of compliant cases with a favourable outcome in the PP populationThe proportion of inappropriate antibiotic prescription in the PP populationThe antibiotic prescription rate in the two arms, in the mITT and PP populationsThe proportion of antibiotic/no antibiotic prescriptions with favourable/unfavourable outcomes

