**Fig. 2 Fig2:**
[figure not shown]
Study participant flow

Patients in the control arm will follow routine diagnostic and treatment procedures for acute febrile illness as outlined in each clinic. Patients in the intervention arm will first be asked to provide information on their attitude towards the use of antibiotics, and then undergo a provisional diagnosis (respiratory/non-respiratory). Samples will be taken from patients to be performed using POCTs and any other tests based on the provisional diagnosis and algorithm. An additional communication package to influence adherence to prescription will be provided by the study team (clinicians, pharmacist and/or nurses) before the patient leaves the facility.

All patients in both the intervention and control arms will be followed up on day 7 (+/− 2) in the health facilities, to reassess their health status and prescription adherence.

Patients who do not improve following the day of enrolment will need to visit the health facilities making an unscheduled visit before the day 7 (+/− 2) follow-up visit for further assessment and management.

The package of POCTs provided in the intervention arm is considered to be an addition to tests provided in routine care. Therefore, where site routine protocols include the use of blood culture or other laboratory tests, these will also be conducted in the intervention arm (along with the normal practice in the control arm). Patients will return to the clinic for review of their prescription in light of these test results, following the normal schedule.

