### Study outcomes

The primary outcome measures are the point estimates of:
The proportion of cases of acute febrile illness with favourable outcome (defined as being alive + no fever + resolution of day 0 symptoms) on day 7, in both arms.The proportion of antibiotic prescriptions for acute febrile illness in the two arms. Specifically, the study intends to detect a reduction (at least 30% from the baseline) in unnecessary antibiotic prescribing, without adversely affecting clinical outcomes. While antibiotic prescription rates are known at the study sites, outcomes are not currently known because patients are not routinely followed-up.

The secondary outcomes are:
Proportion of patients prescribed antibiotics at clinics who describe adherence to prescription on day 7.Proportion of healthcare workers who adhered to new algorithm.Proportion of participants experiencing adverse events (see description in Safety reporting section).

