### Sample size estimation

The sample size calculations were based on criteria that would allow evaluation of antibiotic prescribing at each site.

The sample size was calculated for each country in order to detect a 30% difference (with a 95% confidence interval of +/− 5%) in the antibiotic prescription proportions compared with the initial proportion without the intervention, with a power of at least 80% to detect such a precision estimate (Fig. 3). The minimal theoretical sample size obtained for each site [20] has been increased by 10% to allow for loss to follow-up.

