**Fig. 3 Fig3:**
[figure not shown]
Sample size chart

Estimates of the current proportion of patients prescribed antibiotics for acute febrile illnesses at different clinics in each country study were used as the basis to calculate the required sample size (Table 4).

**Table 4 Tab4:** Baseline antibiotic prescription rates for acute febrile illnesses

Country	Expected antibiotic prescription rate in control arm (based on historic prescribing)	Reduction in prescribing	*N* per arm for children/adolescents	*N* per arm for adults	Total sample size (both arms, including losses to follow-up)
Nepal	55%	30%	1760	1760	3520
Uganda	73%	30%	1200 (combined)		2400
Ghana	43%	30%	1383	n/a	2766
Burkina Faso	77%	30%	859	n/a	1718
Myanmar	43%	30%	440	440	1760
India JSS	50%	30%	864	n/a	1728
India PGIMER	50%	30%	864	864	3456
India RD Gardi	20% (children), 40% (adults)	30%	553	831	2768
India NICED	50%	30%	880	n/a	1760
Total					21,876

Sample sizes are considered a minimum. Enrolment will continue after the sample size has been reached, through the 12 months of the intervention, to allow for seasonal variations.

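### The 30% target is set on unnecessary prescribing but sized and measured on all prescribing, and inappropriate prescribing is assessed only in the per-protocol population

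*Protocol article*

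**What the plan says.** Study outcomes gives the second primary outcome as "The proportion of antibiotic prescriptions for acute febrile illness in the two arms". The next sentence says that the study intends to "detect a reduction (at least 30% from the baseline) in unnecessary antibiotic prescribing, without adversely affecting clinical outcomes". Sample size estimation applies the 30% to a difference "in the antibiotic prescription proportions compared with the initial proportion without the intervention", and the Table 4 column that drives the sizes is headed "Expected antibiotic prescription rate in control arm (based on historic prescribing)". No share of unnecessary prescribing is given anywhere.

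On who can be classified, Participant flow says: "Patients in the control arm will follow routine diagnostic and treatment procedures for acute febrile illness as outlined in each clinic". The same section describes the point-of-care tests as an addition for the intervention arm, and the section on the diagnostic and clinical algorithm confines the algorithm to that arm. Biological specimens says that no samples are kept.

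Analysis of endpoints lists the "proportion of inappropriate antibiotic prescription in the PP" population and no other. The lines beside it, on favourable outcome and on the overall prescription rate, name both mITT and PP and refer to the two arms. Table 5 defines PP by full compliance with the protocol.

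**The concern.** Three things do not fit together.

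- A 30% cut in unnecessary prescribing is a smaller cut in total prescribing, by an amount that depends on a share the article does not state. The target and the basis for the sample size are therefore different quantities.
- A statement about unnecessary prescribing needs each prescription in both arms to be classified on the same basis. The trial's own test results exist in one arm only, and without stored samples they cannot be produced later for controls. No later analysis plan can recover them.
- The only endpoint that addresses appropriateness directly is restricted to a subset defined by behaviour after randomisation. Controls have no algorithm to depart from, so selection into that subset can differ by arm. In the intervention arm it may also remove the very prescriptions that the endpoint should count.

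At stake is the wording of the conclusion. The measured outcome supports a statement about antibiotic prescribing. It does not by itself support a statement about unnecessary prescribing.

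**Working it through.** **Inputs.** From Table 4: control rates p1 and numbers per arm N. From Sample size estimation: 30% reduction, 95% confidence level (taken as two-sided 5%), power of at least 80%, and a 10% increase for losses, so n = N/1.1. Assumed, because the article gives no figure: u, the share of control prescriptions that are unnecessary, from 25% to 100%.

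**The plan's own figures.** The site totals add up: 3520 + 2400 + 2766 + 1718 + 1760 + 1728 + 3456 + 2768 + 1760 = 21,876. The per-arm sizes could not be reproduced from a single formula, so they are taken as given; this point does not rest on them. For a 30% relative fall in all prescribing, these sizes give at least 97% power in every stratum except RD Gardi children, where it is about 72%.

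**Target against sizing.** If only the unnecessary part falls by 30%, the overall relative fall is 0.30 × u:

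- u = 25%: 7.5%
- u = 50%: 15%
- u = 75%: 22.5%
- u = 100%: 30%

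Example at a 50% site with 60% of prescriptions unnecessary: 30 of the 50 points are unnecessary, 30% of 30 is 9, and the total falls to 41%, a relative fall of 9/50 = 18%.

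**Power on all prescribing.** With p2 = p1(1 − 0.30u) and p̄ the mean of p1 and p2,

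power = Φ{[p1 − p2 − 1.96√(2p̄(1 − p̄)/n)] / √[(p1(1 − p1) + p2(1 − p2))/n]}.

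Three strata at u = 50%:

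- Myanmar, each stratum: n = 440/1.1 = 400; 43.0% to 36.55%; (0.0645 − 1.96 × 0.03461)/0.03453 = −0.10; power 46%.
- RD Gardi children: n = 553/1.1 = 503; 20% to 17%; (0.030 − 1.96 × 0.02449)/0.02447 = −0.74; power 23%.
- RD Gardi adults: n = 831/1.1 = 755; 40% to 34%; (0.060 − 1.96 × 0.02484)/0.02479 = 0.46; power 68%.

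All strata:

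| Stratum | u = 25% | u = 50% | u = 75% | u = 100% |
|---|---|---|---|---|
| Nepal | 65% | 99.7% | >99% | >99% |
| Uganda | 80% | >99% | >99% | >99% |
| Ghana | 38% | 91% | 99.9% | >99% |
| Burkina Faso | 74% | 99.9% | >99% | >99% |
| Myanmar, each stratum | 15% | 46% | 80% | 97% |
| JSS; PGIMER, each stratum | 32% | 85% | 99% | >99% |
| RD Gardi children | 9% | 23% | 46% | 72% |
| RD Gardi adults | 22% | 68% | 96% | 99.9% |
| NICED | 32% | 85% | 99.5% | >99% |

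The Nepal row uses 1760 per arm, as printed. Two strata of that size would total 4 × 1760 = 7040, not 3520. If 1760 is instead the total for both arms of a stratum, n = 880/1.1 = 800 and power at u = 50% (55% to 46.75%) is Φ[(0.0825 − 1.96 × 0.0250)/0.0249] = 91%, which leaves the reading of the table unchanged.

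**Population for inappropriate prescribing.** No arithmetic applies here; the passages have to be set side by side. Table 5 admits to PP only those in full compliance. Following the algorithm is what the protocol asks for in the intervention arm, and the section on adherence strategies judges algorithm adherence partly by the antibiotic prescribed. If PP compliance includes that, and if inappropriate means against the algorithm, then a patient given an antibiotic despite an 'N' result leaves PP, and the count in the intervention arm loses those events. The legend to Fig. 1 also has a discretionary outcome, 'P'. A prescription made there follows the algorithm and stays in PP.

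**The case against.** The strongest reply is that the primary comparison is sound. The overall prescription rate is named as the outcome, is the quantity sized, and is compared between randomised arms. Need for antibiotics is balanced in expectation, so a lower total with no worse clinical outcome is a coherent indirect argument about unnecessary use. This stands, and it limits the point to the wording of the target and to one further endpoint.

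A reader might infer that inappropriate prescribing in PP is zero in the intervention arm by construction. The article does not support that. It never says that PP requires the health worker to follow the algorithm: Table 5 speaks of participants, algorithm adherence is a separate secondary outcome, and a further line counts compliant cases within PP, which would be redundant if PP already removed every kind of non-compliance. Nor does it say that appropriateness is judged by the algorithm, and 'P' cases would remain in any event. The line is also not worded as a comparison of arms. Exact PP criteria and the definition of inappropriate may properly sit in the analysis plan. What remains is the stated choice of PP alone.

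A reader might also infer that the trial as a whole is underpowered. It is not: in the 50% to 41% example, with 864/1.1 = 785 per arm, power is about 95%. The Table 4 sizes are minima, and enrolment continues for 12 months, so achieved power may be higher than tabulated.

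**Conclusion.** The point holds in a limited form. The target and the sized outcome are different quantities unless every control prescription is unnecessary. How much that costs depends on the assumed share u. At 50%, power falls below 80% only in Myanmar and at RD Gardi, taking strata separately and at the minimum sizes. At 25%, every stratum is at or below about 80%. At 100%, only RD Gardi children fall short.

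Need cannot be classified on the trial's test-based standard in both arms; that follows directly from the text. Inappropriate prescribing is assigned to PP alone, a subset formed after randomisation. The push towards zero in the intervention arm is conditional on two definitions that the article leaves open, and is not established as fact. The between-arm comparison of overall prescribing is not affected.

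**What to change.** - In Study outcomes, state the target as a 30% relative reduction in the proportion of patients prescribed any antibiotic, intervention against control, in all randomised participants. Word the conclusion as antibiotic prescribing, without the qualifier 'unnecessary'.
- In Analysis of endpoints, report inappropriate prescription descriptively in all randomised intervention patients, not in PP alone, defined as an antibiotic prescribed against an algorithm 'N' result. The case report form review already planned for algorithm adherence supplies the data.
- If a between-arm version is wanted, apply one rule in both arms that uses only day-0 information recorded in both, such as history, examination and routine tests.

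The cost is a narrower claim and a few lines of text. No new data are needed.

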### Other analyses

We will calculate the combined proportion of compliant participants with favourable outcomes and non-compliant participants with unfavourable outcomes within each arm.

Additionally, the ratio of the proportion of compliant participants with a favourable outcome versus the proportion of non-compliant participants with an unfavourable outcome will be reported as relative risk.

There is no planned interim analysis.

### Handling of missing data

Missing and invalid data for key measures that contribute to the evaluation of each of the outcomes will be reported in summary tables and will not be imputed. The primary outcomes do not involve quantitative assessments, and therefore, we feel it would not be appropriate to input data. Data from participants for whom partial data are available will be included in the analysis of specific outcomes, provided the data allow to evaluate them (e.g. adherence to prescription).

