### Strategies to improve and assess adherence

Patients and caregivers in the intervention arm (but not the control arm) will receive a communication message in support of adherence to the prescription, based on the local research findings described above. The method of delivery of the communication message will be site-specific, depending on the roles of different types of healthcare workers, and the behavioural determinants identified in the qualitative analysis.

The delivery of the core communication message will be personalized to the individual patient (e.g. adjusting emphasis, but not message content), based on a small amount of information collected from the patient before clinical assessment.

All patients in both the intervention and control arms will be followed up on day 7 (+/− 2) in the health facilities to reassess their health status and adherence to prescription. Information on adherence to prescription will be collected using qualitative in-depth interviews with the patient and through pill counts (participants/caregivers will be asked to bring back packaging and remaining medicine on day 7). This includes assessing the behaviour of patients who were not prescribed medication to find out if they obtained any antibiotics or any other treatment, the reasons for this and where the antibiotics or other treatment were obtained.

All enrolled participants (and caregivers, in case of children) will be reminded prior to departure on day 0 to visit the health facilities if their illness worsens before day 7. All participants who do not return on day 7 will be followed up via telephone to assess their well-being and the need to return to the clinic for the end of study assessment. Where feasible and where consent was provided by study participants at enrolment, the investigators will conduct home visits if the patient is unable to return to the clinic for the day 7 follow-up visit.

Adherence to the diagnostic algorithm will be evaluated by reviewing the case report forms (CRFs) to assess algorithm-driven use of POCTs and antibiotic prescriptions.

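### The day-7 clinical outcome is left unimputed because it is not quantitative, an invalid reason that leaves the arm comparison on observed outcomes only

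*Protocol article*

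**What the plan says.** The section Handling of missing data states that missing or invalid data on the key outcome measures "will be reported in summary tables and will not be imputed". The justification follows at once: "The primary outcomes do not involve quantitative assessments, and therefore, we feel it would not be appropriate to input data". I read the printed word input as impute, in line with the sentence before it. The section then adds: "Data from participants for whom partial data are available will be included in the analysis of specific outcomes, provided the data allow to evaluate them". Taken together, this is an available-case rule applied outcome by outcome.

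The rule bears mainly on the first of the two primary outcomes in Study outcomes, a favourable result "defined as being alive + no fever + resolution of day 0 symptoms) on day 7, in both arms". The same section gives that outcome its role: prescribing should fall "in unnecessary antibiotic prescribing, without adversely affecting clinical outcomes". Under Sample size estimation, the minimum size "has been increased by 10% to allow for loss to follow-up". Strategies to improve and assess adherence provides for tracing: "All participants who do not return on day 7 will be followed up via telephone to assess their well-being". That sentence goes on to the need to come back for the final assessment, and the section adds home visits where feasible and consented.

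**The concern.** The rule and its reason are both stated outright, so this is not a detail left to an SAP that is not shown. Declining to impute can be defended, but only with an argument about why data are missing. The type of variable is not such an argument. Binary outcomes can be multiply imputed with a logistic model, counted as unfavourable, or bounded by extreme cases.

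Efficacy analyses describes point estimates with Wilson intervals and no covariate model. With unadjusted proportions among observed patients, the arm difference is unbiased only if missingness within each arm is unrelated to outcome. The analysis populations do not help: Analysis of endpoints reports this outcome in the mITT and PP sets, and neither supplies a value for a patient whose day-7 status is unknown.

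At stake is the trial's check that less prescribing does not worsen recovery. The section on the data and safety monitoring board accepts that the algorithm may miss a need for antibiotics in some intervention patients. If such patients worsen and seek care elsewhere, they may be the ones missing. The trial is also open label, so return could differ by arm.

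**Working it through.** **Inputs from the article.** 1:1 allocation; 10% loss allowance; 864 per arm at India JSS with a 50% control prescribing rate; total 21,876. The favourable-outcome rate is not given: "outcomes are not currently known because patients are not routinely followed-up".

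**Assumed inputs.** 90% favourable among returners (85% to 95% for sampling error), and 50% to 100% among non-returners.

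**1. The plan's own figure.** n = (1.96 + 0.8416)² × p(1 − p) / 0.05². At p = 0.50, n = 7.849 × 0.25 / 0.0025 = 785, and 785 × 1.10 = 864, as in Table 4. The 10% is therefore an inflation of n. Over the trial it is 21,876 − 21,876/1.10 ≈ 1,989 patients.

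**2. Sampling error.** The 95% half-width of the arm difference is 1.96 × √(2p(1 − p)/n), a normal approximation.
- n = 785, p = 0.90: 1.96 × √(0.18/785) = 0.030, or 3.0 points.
- p = 0.85 gives 3.5 points and p = 0.95 gives 2.2 points.
- At p = 0.90, n = 400 gives 4.2 points and n = 1,600 gives 2.1 points.

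**3. Bias when the observed difference is 0.** With loss l in an arm, the true arm rate is (1 − l) × 0.90 + l × q, where q is the favourable rate among non-returners.

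| Loss, intervention vs control | q | Intervention | Control | True difference |
|---|---|---|---|---|
| 12% vs 8% | 0.60 | 0.864 | 0.876 | −1.2 points |
| 15% vs 5% | 0.60 | 0.855 | 0.885 | −3.0 points |
| 10% vs 5% | 0.50 | 0.860 | 0.880 | −2.0 points |
| 10% vs 5% | 0.70 | 0.880 | 0.890 | −1.0 point |
| 10% vs 10% | same q in both arms | equal | equal | 0 |
| 15% vs 5% | 1.00 | 0.915 | 0.905 | +1.0 point |

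Swapping the two loss rates reverses the sign. Unequal loss is not required: at 10% loss in both arms, if missing intervention patients do 20 points worse than missing controls, the shift is 0.10 × (−0.20) = −2.0 points.

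**4. Worst/best-case bounds.** With loss l in each arm and observed difference d, the bounds are (1 − l) × d ± l. At d = 0 they are ±10 points for 10% loss, ±5 for 5% and ±2 for 2%.

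**The case against.** Several points on the other side stand.

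- **Tracing.** Non-returners are telephoned, recalled to clinic and, where possible, visited at home. Willingness to return on day 7 is an entry criterion. Actual loss may be well below 10%. A reader might infer that telephone answers are barred from the outcome analysis. The article does not say so; it is silent, and its partial-data sentence could admit them. What remains missing still falls under the no-imputation rule.
- **Differential return.** The extra message in the intervention arm concerns adherence to the prescription, not attendance, and follow-up is the same in both arms. Differential loss is possible; nothing suggests that it is expected.
- **Labels.** A reader might call this a safety endpoint. It is a primary clinical outcome. Adverse events are a secondary outcome, and the board reviews deaths, hospitalisations and losses by arm.
- **Size against a margin.** A reader might infer that the bias matches the harm the trial must exclude. The article states no harm margin, so that comparison cannot be made.
- **Remedy.** Imputation by arm under missing-at-random would not by itself remove the bias shown, because those scenarios let non-returners do worse for unmodelled reasons.
- **SAP.** Sensitivity analyses are commonly left to the SAP, so their absence from the article is not the finding. The finding is the stated rule and its stated reason.

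**Conclusion.** The point holds in a limited form. The article commits to not imputing the day-7 favourable outcome and gives a reason that is statistically wrong. The comparison would then rest on observed outcomes alone.

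With loss averaging 10%, the assumed patterns with 60% favourable among non-returners hide about −1 to −3 points behind an observed difference of 0. The larger figure equals the sampling half-width of about 3 points at 785 per arm. The ±10-point bounds are extremes that require every missing patient to succeed in one arm and fail in the other; they show what the data alone cannot exclude, not a likely error.

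These sizes depend on assumed favourable rates and loss patterns. The bias is nil if loss and non-returner outcomes are the same in both arms, and it changes sign if recovered patients are the ones who stay away. Pooling sites would reduce sampling error but not a bias that runs the same way across them. Prescribing is recorded on day 0 and is largely unaffected.

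**What to change.** 1. Delete the not-quantitative reasoning and the blanket rule against imputation.
2. State that alive, fever and symptom status obtained through the telephone or home contact already planned counts as day-7 outcome data, flagged by mode of collection.
3. Keep the observed-case analysis, and accompany it with a tipping-point analysis that varies the favourable rate among non-returners separately by arm, together with worst/best-case bounds.
4. Add multiple imputation by arm as a supporting analysis, using site, age group, respiratory or non-respiratory presentation, day-0 antibiotic and unscheduled visit. Presentation should be derived in the same way in both arms from the day-0 history and examination.

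The cost is a paragraph in the SAP, a little more analysis work, and making sure that the existing call asks the three outcome questions. No change to sample size or visits is needed.
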